### Criteria

#### Inclusion criteria

Participants meeting all of the following criteria will be enrolled: (1) inpatients or outpatients with GAD diagnosed in accordance with the International Classification of Disease-10; (2) those with a diagnosed TCM pattern of liver-qi stagnation transforming into fire, which usually manifests as irritability, constriction in the chest, hypochondriac distention, gastric discomfort with acid regurgitation, dry mouth or bitter taste in the mouth (or both), constipation, headache, conjunctival congestion, tinnitus, reddened tongue with yellow fur, and rapid pulse; (3) ages between 18 and 65 (no limitation on gender); (4) Hamilton Anxiety Rating Scale (HAM-A) scores between 14 and 39 (inclusive) at screening and baseline; and (5) written informed consent obtained either personally or by proxy.

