### Outcome measurements

Outcome measurements are scheduled at screening, baseline, and the end of weeks 1, 2, 4, and 8.

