### Sample size calculation

As there is no large randomized controlled trial of SGQR formula for GAD, we referred to the experience of experts in this field. A response rate of 91% for SGQR was assumed. As to buspirone, the response rate was about 75%, according to the literature [16]. In the setting of α = 0.05 and β = 0.2, the sample size was calculated to be 83 in each group. Given a 20% dropout rate, 17 more participants will be required in each group. In total, 200 participants will be enrolled.

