### Data management and analysis

CRFs will be entered by two independent researchers and supervised by a third one to ensure accuracy. Data analysis will be performed by statisticians who are blind to the randomization by using SPSS (Statistical Product and Service Solutions) Statistics for Windows, version 20.0 (IBM Corp., Armonk, NY, USA). Continuous variables will be presented as mean and standard deviation, and categorical variables will be presented as frequency or percentage. Demographic data and outcome measurements at baseline will be listed to ensure relatively even baseline levels. A *t* test (if normally distributed) or non-parametric test (if not normally distributed) will be used for continuous variables when conducting baseline comparisons. The repeated measures ANOVA (analysis of variance) will be used when analyzing the primary and secondary outcomes. Chi-squared or non-parametric test will be applied for categorical variables. The analysis of efficacy will be performed in accordance with the intention-to-treat principle. Missing values will be imputed by the last observation carried forward method. Subgroup analysis will be conducted if necessary. A *P* value of less than 0.05 will be considered statistically significant. A mixed-effects model for repeated measures will be performed as a sensitivity analysis of the primary efficacy outcome.

Mid-term date analysis will be conducted after half of the recruitment is finished, and the principal investigator will decide whether any measure should be taken in light of the results. All of the data will be deposited in the platform developed by our team. Anding Hospital will be responsible for the data, and other researchers can have access to the data only after application and permission.

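### Repeated measures ANOVA on LOCF-filled scores is the main analysis of every scale and the mixed model only a sensitivity check of HAM-A; the mixed model should lead and also cover HAMD-17 and the TCM scale

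*Protocol article*

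**What the plan says.** The relevant statements are in the protocol article, mostly under Data management and analysis.

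- Main method: "The repeated measures ANOVA (analysis of variance) will be used when analyzing the primary and secondary outcomes".
- Missing data: "Missing values will be imputed by the last observation carried forward method".
- Threshold: a P "value of less than 0.05 will be considered statistically significant".
- Mixed model: "A mixed-effects model for repeated measures will be performed as a sensitivity analysis of the primary efficacy outcome".
- Visits (Outcome measurements): "Outcome measurements are scheduled at screening, baseline, and the end of weeks 1, 2, 4, and 8".
- Entry range for HAM-A (Inclusion criteria): "scores between 14 and 39 (inclusive) at screening and baseline". The exclusion criteria also bar patients with a HAMD-17 score above 7 at screening.
- Size (Sample size calculation): 200 patients, so 100 per arm, with 20% dropout expected.

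The article does not mention sphericity or a degrees-of-freedom correction. It does not say whether the group main effect, the group-by-time interaction or a single visit decides, or whether baseline is one of the repeated measures. It gives no standard deviations or correlations for any visit.

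**The concern.** The within-subject tests of a repeated measures ANOVA (time and group-by-time) keep their nominal level only under sphericity, meaning that the difference between any two visits has the same variance. A mixed model with unstructured covariance does not need that condition, and it uses the observed scores without copying them forward. The plan includes such a model type but ranks it second, and only for HAM-A. HAMD-17 and the TCM scale rest on ANOVA with LOCF alone.

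There is reason to doubt sphericity. Over visits at weeks 0, 1, 2, 4 and 8, scores close in time may well correlate more than scores far apart. Entry limits on HAM-A and HAMD-17 may also narrow the early spread relative to later visits. If the interaction were tested without a correction, its P value would then be too small, and a false claim that SGQR and buspirone differ in course would be more likely than the stated 5%. On the two secondary scales no other planned analysis would show this.

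**Working it through.** **Inputs from the article.** 100 per arm, no true difference (null), k = 5 visits at weeks 0, 1, 2, 4 and 8, α = 0.05, dropout 0% or 20% with LOCF.

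**Inputs assumed.** Compound symmetry with correlation 0.5; correlation falling by 0.6 to 0.8 per visit or 0.7 to 0.95 per week; SD constant, or rising from 4 to 8. Dropout is completely at random, and mean scores fall over the 8 weeks.

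**Formulas.** Let d_j be the arm difference in means at visit j, d̄ its average, S the pooled within-arm covariance matrix, and C the centring matrix.

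- Group-by-time: F = [(n/2) Σ(d_j − d̄)² / (k−1)] / [tr(CSC)/(k−1)], referred to 4 and 4 × 198 = 792 degrees of freedom.
- Greenhouse-Geisser: both degrees of freedom are multiplied by ε = [tr(A)]² / [(k−1) Σ a_ij²], where A = CSC. Sphericity is ε = 1.
- Group main effect: F = (n/2) d̄² / (mean of all entries of S), on 1 and 198 degrees of freedom.

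**Step 1, the stated 5%.** Under compound symmetry without dropout, on this same uneven schedule, the uncorrected group-by-time test rejects in 4.9% of null trials. The stated level is reproduced when sphericity holds.

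**Step 2, why decay matters.** With constant variance σ², the difference between two visits has variance 2σ²(1 − r). With r = 0.90 per week:

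- weeks 1 and 2: 2σ²(1 − 0.90) = 0.20σ²
- weeks 0 and 8: r = 0.90⁸ = 0.43, so 2σ²(1 − 0.43) = 1.14σ²

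The ratio is 5.7. Under compound symmetry at 0.5 both variances equal σ², whatever the spacing. The correlation pattern therefore breaks sphericity, and the uneven gaps alone do not.

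**Step 3, simulated type I error at nominal 5%** (8000 trials per scenario, Monte Carlo SE about 0.25 to 0.3 points). ε is the value for complete data.

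| Pattern | ε | Uncorrected, no dropout | Uncorrected, 20% LOCF |
|---|---|---|---|
| Compound symmetry 0.5 | 1.00 | 4.9% | 5.9% |
| Same, rising SD | 0.87 | 5.7% | 6.0% |
| 0.6 per visit | 0.75 | 5.7% | 7.0% |
| 0.8 per visit | 0.63 | 6.9% | 8.0% |
| 0.7 per visit, rising SD | 0.62 | 7.2% | 7.8% |
| 0.7 per week | 0.75 | 6.4% | 7.2% |
| 0.90 per week | 0.58 | 7.9% | 8.7% |
| 0.95 per week | 0.54 | 8.2% | 8.8% |
| 0.90 per week, rising SD | 0.53 | 8.6% | 8.6% |

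Across all rows the Greenhouse-Geisser test rejects in 4.2% to 5.4% and the group main effect in 4.5% to 5.6%. With the four post-baseline visits only (0.90 per week, no dropout), the uncorrected test gives 7.1%.

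**Step 4, repeat of the key cases.** A separate simulation gave 7.7% to 8.8% uncorrected for decay of 0.90 to 0.95 per week, 4.6% to 4.9% with Greenhouse-Geisser, and about 5% for an unstructured multivariate test. Under compound symmetry it gave 4.8% without dropout and 5.0% with 20% LOCF.

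**Step 5, the LOCF figure under compound symmetry (5.9% against 5.0%).** Under the null, F behaves as Σλ_iχ²₁/Σλ_i, with λ_i the non-zero eigenvalues of CSC and S the covariance after LOCF. This direct calculation, allowing for the estimated denominator, gives 5.0% if mean scores are flat and 5.4% if they fall as in Step 3 (24, 20, 17, 13, 10 with SD 6). The rest of the 5.9% is compatible with simulation error. LOCF alone therefore adds less than half a point here.

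**The case against.** The strongest reply is that the article is silent rather than wrong. Repeated measures ANOVA covers corrected as well as uncorrected tests, and the choice among them is commonly left to an analysis plan or full protocol, neither of which is shown. A reader might infer that the ANOVA will be run uncorrected, or that the visit schedule and LOCF rule out sphericity so that the test must run at 6% to 9%. The documents support neither. No correction is excluded, and on the same schedule compound symmetry gives about 5%. A further set of 24 scenarios did give 6.1% to 9.0%, but all of them assumed decaying correlation (0.80 to 0.95 per week), so the near-nominal case was left out. The entry limits do not settle the matter either: the HAM-A window spans 39 − 14 = 25 points of a 0 to 56 scale, and nothing in the article shows how far that compresses the baseline spread.

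It is also fair to say that the group main effect keeps its level, that a comparison at one visit would not be the affected test, and that HAM-A already has a mixed-model check.

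All of this stands, and a missing correction would be no finding by itself. What the reply leaves untouched is the order of methods, which the article does state: ANOVA with LOCF first for every scale, and the mixed model second and for HAM-A only. An unseen plan that merely added a correction would not change that order.

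**Conclusion.** The point holds as an improvement to a stated choice of method, not as a demonstrated error in the type I error rate. The possible inflation rests on three conditions that the article does not state: the group-by-time test is the one relied on, no correction is applied, and correlation decays over time. If all three hold, the true level is about 8% to 9% for decay of 0.90 to 0.95 per week, at most 8.8/5 ≈ 1.8 times the nominal rate in the table above. Under compound symmetry it stays near 5%. The group main effect is not affected in any scenario.

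The consequence is greatest for HAMD-17 and the TCM scale, which have no planned mixed model. Any bias in the treatment estimate from carrying scores forward was not quantified here.

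**What to change.** Under Data management and analysis:

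- Make a mixed model for repeated measures with unstructured covariance, fitted to the observed data, the main analysis of HAM-A.
- Use the same model for HAMD-17 and the TCM scale.
- Keep repeated measures ANOVA with LOCF as a sensitivity analysis, and state that any within-subject test (time, group-by-time) uses the Greenhouse-Geisser correction.

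This takes a sentence or two and no extra visits or data, and the model type is already planned for HAM-A. The cost is a little more analysis work and slightly larger P values than an uncorrected test would give.

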## Background

Generalized anxiety disorder (GAD) is a persistent and common disorder characterized by feelings of threat, restlessness, irritability, sleep disturbance, tension, and symptoms such as palpitations, dry mouth, and sweating [1]. An epidemiological study in China suggested that the illness has a lifetime prevalence of 0.3% and a 12-month prevalence of 0.2% (the highest prevalence is in the 50- to 64-year-old group) but shows no gender difference [2]. The high prevalence of concurrent psychiatric disorders makes the diagnosis of GAD difficult, possibly contributing to the different epidemiological results of China, Europe, and the US [3, 4]. Comorbidity with at least one other mental disorder at some point troubles the majority of patients with GAD, most commonly with major depressive disorder [1, 5]. Besides, GAD is associated with considerable economic costs owing to work productivity loss and high medical resource use. The role impairments of pure GAD are similar in magnitude to those of major depressive disorder [5].

GAD has a relapsing course, and treatments rarely result in complete resolution of symptoms. In the short to medium term, effective intervention includes psychological therapies, such as cognitive behavioral therapy; self-help approaches based on cognitive behavioral therapy principles; and pharmacological treatments [1]. Until the mid-1980s, pharmacological treatment options consisted primarily of benzodiazepines, which later became an effective short-term therapy in consideration of their abuse potential. For patients requiring long-term treatment, buspirone and some newer antidepressants became the alternatives. Nevertheless, the mild efficacy combined with a slow onset of action dampened the satisfaction with buspirone, whereas antidepressants, mainly selective serotonin reuptake inhibitors (including paroxetine), brought both efficacy and lots of adverse effects [6]. The search for the ideal anxiolytic has never stopped.

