#### Primary outcome

HAM-A, which is one of the first and most widely used rating scales to measure the severity of anxiety symptoms, will be set as the primary outcome [7]. There are 14 items in the HAM-A, which incorporate groups of symptoms (such as fears, autonomic symptoms, and respiratory symptoms) rather than specific, single symptoms. Each item is rated from 0 to 4; the higher the score, the worse the situation. The good reliability and validity of HAM-A make it a standard interviewer-administered instrument [8].

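### LOCF feeds the main repeated measures ANOVA and the mixed model is only a sensitivity analysis; the ranking should be reversed, because LOCF biases the comparison if dropout differs between arms and shrinks an effect that grows over time

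*Protocol article*

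**What the plan says.** All of the analysis rules are in the protocol article, Data management and analysis. The main method is fixed as follows: "The repeated measures ANOVA (analysis of variance) will be used when analyzing the primary and secondary outcomes". The population is fixed too: "The analysis of efficacy will be performed in accordance with the intention-to-treat principle". For incomplete data: "Missing values will be imputed by the last observation carried forward method". No other imputation is named, so LOCF supplies the missing values for the main ANOVA of every efficacy outcome. The alternative is ranked below it: "A mixed-effects model for repeated measures will be performed as a sensitivity analysis of the primary efficacy outcome". Secondary outcomes have no such alternative, and no rule says which result prevails if the two primary-outcome analyses disagree.

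Two other sections matter. Outcome measurements gives the visits: "Outcome measurements are scheduled at screening, baseline, and the end of weeks 1, 2, 4, and 8". Sample size calculation makes one allowance for loss, the same for both arms: "Given a 20% dropout rate".

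**The concern.** LOCF assumes that a participant who leaves after week 1, 2 or 4 would have had the same HAM-A score at week 8. The sample size section assumes response rates of 91% and 75%, which imply that most participants in both arms improve substantially. If scores keep falling to week 8, a carried-forward score is on average too high. The arm that loses more participants, or loses them earlier, then looks worse for that reason alone.

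An effect that builds up over the 8 weeks is also diluted, because those who leave contribute the smaller early difference. With 100 per arm, the allowed dropout means about 20 participants per arm carrying such values. The main P value could then partly reflect who leaves and when, although the plan already contains an analysis that does not freeze those scores.

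**Working it through.** **The plan's own figure.** The article gives no number for the effect of LOCF. The nearest stated figure, 83 per group, reproduces with the unpooled two-sided formula: (1.960 + 0.842)² × [0.91×0.09 + 0.75×0.25] / 0.16² = 7.849 × 0.2694 / 0.0256 = 82.6, so 83. It rests on response rates, so changing the missing-data method leaves the stated N as it is.

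**Inputs.** From the article: visits at baseline and weeks 1, 2, 4 and 8; 200 participants at 1:1, so 100 per arm; 20% dropout. Assumed, because the article does not give them: mean HAM-A of 24, 21, 18, 14 and 11 at those five visits, SD 7, correlation 0.6 between visits, and dropouts leaving after week 1, 2 or 4 with equal chance. Dropout is written SGQR/buspirone, and differences are SGQR minus buspirone.

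**Bias with no true effect.** The improvement a dropout still has to come is on average [(21−11) + (18−11) + (14−11)]/3 = 20/3 = 6.67 points. The false week-8 difference is (SGQR dropout − buspirone dropout) × 6.67:

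- 20%/20%: 0
- 18%/22%: −0.04 × 6.67 = −0.27
- 15%/25%: −0.10 × 6.67 = −0.67
- 10%/30%: −0.20 × 6.67 = −1.33

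Swapping the two rates reverses the sign. Simulation gives the same values (about −0.67 and −1.34 for the last two).

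**False-positive rate of the planned ANOVA** (five visits, simulated, nominal 5%):

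| Dropout | Group-by-time | Group main effect |
|---|---|---|
| 20%/20% | about 5% | about 5% |
| 18%/22% | about 6% | about 5% |
| 15%/25% | 9 to 10% | about 6% |
| 10%/30% | 26 to 28% | 8 to 9% |

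The main effect suffers less because it averages over visits that LOCF hardly touches. At 10%/30% the bias is 0 at baseline and week 1, 0.20 × (1/3) × 3 = 0.20 at week 2, 0.20 × (1/3) × (7 + 4) = 0.73 at week 4 and 1.33 at week 8. The mean is (0 + 0 + 0.20 + 0.73 + 1.33)/5 = 0.45 points.

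**True effect that grows.** Assume differences of −0.75, −1.5, −2.25 and −3.0 at weeks 1, 2, 4 and 8, with 20% dropout in both arms. LOCF targets 0.80 × (−3.0) + 0.20 × (−0.75 − 1.5 − 2.25)/3 = −2.4 − 0.3 = −2.7.

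**Standard errors.** In these runs the nominal LOCF standard error (0.89 to 0.92) matches the empirical SD of the estimate (0.87 to 0.92).

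**A second set of assumptions.** With means 24, 21, 18, 14 and 10, SD 5 to 7, and dropout either completely at random or depending on the last observed score, the bias was 0.8 to 1.0 points at nominal 15%/25% and 1.6 to 2.1 at 10%/30%. Group-by-time rejection was 12% to 22% and 33% to 58%. A maximum-likelihood analysis, fitted in the runs with exchangeable correlation, stayed within 0.04 points of the truth.

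**The case against.** The strongest reply is that the plan already includes the better analysis for the primary outcome, so a result driven by LOCF would be exposed. That is partly right and lowers the severity. It does not settle the matter: the headline result remains the LOCF one, nothing says what happens on disagreement, and the secondary outcomes have no check.

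Second, the article predicts no imbalance in dropout. This stands. At 20%/20% with no effect at any visit the error rate is nominal, and at 18%/22% it is barely raised. The larger figures are conditional on imbalance and on an assumed HAM-A course.

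Third, LOCF is often defended as conservative. At equal dropout it does shrink a growing effect. But in the second set of assumptions a true −3 was estimated as about −3.6 at 15%/25% and about −1.8 at 25%/15%, so it cannot be relied on to be conservative.

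Three stronger readings are tempting and are not supported:

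- A reader might infer that single imputation makes the standard errors too small. In these runs it did not; poor interval coverage came from bias.
- A reader might infer from the Background ("the mild efficacy combined with a slow onset of action dampened the satisfaction with buspirone") that LOCF must penalise buspirone most. That sentence sets buspirone against other drug classes, and the article says nothing about how quickly SGQR acts, so no direction follows.
- A reader who simulates a week-8 ANCOVA will find error rates of about 12% at a 25%/15% split and 33% at 30%/10%. The article plans a repeated measures ANOVA, whose inflation is smaller under the same assumptions and depends on the term tested.

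**Conclusion.** The concern holds as a question of ranking and of conditional bias. Under the main assumptions the week-8 bias runs from nil at equal dropout to about 1.3 points at a 10%/30% split, in either direction, and a growing effect of 3 points loses about a tenth of its size at equal 20% dropout. Whether the P value is affected depends on the ANOVA term: group-by-time is exposed, the group main effect only slightly. All of this rests on HAM-A continuing to fall between the early visits and week 8, which the article implies but does not quantify. The harm is bias and not understated uncertainty. This should be fixed, but because the mixed model is already planned it does not invalidate the design.

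**What to change.** Make the planned mixed model for repeated measures the primary analysis, using all observed HAM-A scores without imputation, with the week-8 treatment contrast as the primary estimate. Use the same model for the continuous secondary outcomes that are measured repeatedly. Keep the LOCF repeated measures ANOVA as a sensitivity analysis.

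The model relies on data being missing at random: given their observed scores, those who leave would have continued like similar participants in their arm. One sensitivity analysis that departs from this, such as delta-adjusted imputation, would probe it.

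The cost is modest but goes beyond wording. Ethical issues requires a written application to the ethics committee for protocol changes, and Quality control requires permission from the primary researcher. The article reports recruitment as ongoing and plans a mid-term analysis whose results go to the principal investigator. The amendment should therefore be dated and made before unblinding, with a record of whether any mid-term results had been seen. No extra participants or visits are needed.

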### Randomization and allocation concealment

Eligible participants will be randomly assigned to either the study group or the control group in a ratio of 1:1. A computer-generated random allocation sequence will be produced by an independent statistician using SAS software (SAS Institute, Cary, NC, USA). Based on the allocation sequence, drug packages will be labeled serially. Participants will receive the corresponding drug package in the order of recruitment. The complete random sequence will be kept by the primary researcher in Beijing Anding Hospital. Emergency envelopes containing the random allocation individually will be prepared for each center, which can be unsealed only in the case of serious adverse events.

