### Blinding

Pharmacists in charge of labeling the drug packages do not take part in the conduction of the trial. Participants and researchers responsible for screening, recruitment, dispensing medicine, and outcome assessment will all be blind to the group allocation. Statistical analysis will be conducted by independent statisticians who will know only the group codes but not the corresponding interventions.

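### The mid-term analysis is not limited to pooled or safety data, the principal investigator acts on its results, and the only threshold is P<0.05

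*Protocol article*

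**What the plan says.** Under Data management and analysis, the Protocol article describes between-group methods for the efficacy outcomes and sets one criterion: a P "value of less than 0.05 will be considered statistically significant". The next paragraph schedules a mid-term analysis once half of recruitment is finished and says that "the principal investigator will decide whether any measure should be taken in light of the results". It gives no purpose for the look and does not restrict it to pooled or safety data.

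Three other sections bear on this:

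- **Blinding.** Participants and the researchers who screen, recruit, dispense and assess are blind. On the analysts: "Statistical analysis will be conducted by independent statisticians who will know only the group codes but not the corresponding interventions".
- **Randomization and allocation concealment.** The complete random sequence is kept by the primary researcher at the lead hospital.
- **Ethical issues.** Any change to the protocol goes by written application to the research ethics committee, which decides whether it is acceptable.

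The sample size section gives a single calculation: "In the setting of α = 0.05 and β = 0.2, the sample size was calculated to be 83 in each group".

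**The concern.** The text settles three things together: a look at the data at half recruitment, a decision maker who is the trial's own principal investigator, and a decision that depends on the results. With one flat threshold, two problems follow if the look compares the arms.

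**Error rate.** If efficacy could be claimed at P<0.05 mid-term and, failing that, tested again at P<0.05 at the end, the trial has two chances of a false positive. The 5% in the plan would then not be its real error rate.

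**Interim knowledge.** HAM-A is interviewer-administered. From week 2 researchers adjust the dosage, and they may alternate between low and high dosage according to the patient's reaction. Anyone involved in the conduct of the trial who knows that one coded group is ahead could influence recruitment, dosing decisions or ratings in the second half, even without intending to.

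**Working it through.** **1. Reproduce the plan's own figure.** Inputs from Sample size calculation: "A response rate of 91% for SGQR was assumed"; for buspirone "the response rate was about 75%, according to the literature"; α = 0.05 and β = 0.2. Allocation is 1:1. Sidedness is not stated; two-sided is assumed because it reproduces the figure. With the unpooled two-proportion formula:

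n = (1.960 + 0.842)² × (0.91×0.09 + 0.75×0.25) / (0.91 − 0.75)² = 7.849 × 0.2694 / 0.0256 = 82.6, rounded up to 83.

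Other two-sided variants give 82 (arcsine), 86 (pooled variance) and 98 (continuity-corrected). One-sided variants give 65 to 80. So 83 is what a single-look design at two-sided 0.05 requires. This is only supporting evidence: an O'Brien-Fleming allowance adds about one participant per group (step 4), too little for the sample size alone to settle the question.

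**2. Information at the look.** The trigger is half of recruitment, not half of completed follow-up. Treatment lasts 8 weeks, so the latest recruits will have no week-8 value. The information fraction t is therefore at most about 0.5. The documents give no figure, so 0.25 to 0.5 is taken as an assumed range.

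**3. Error rate with P<0.05 at both looks.** Under no difference, the two standardised test statistics are bivariate normal with correlation √t. The chance that at least one exceeds 1.96 in absolute value is

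0.05 + 0.05 − P(both exceed).

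| t | P(both exceed) | Overall error |
|---|---|---|
| 0.50 | 0.0169 | 0.0831 (8.3%) |
| 0.40 | 0.0137 | 0.0863 (8.6%) |
| 0.25 | 0.0093 | 0.0907 (9.1%) |

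A look that can stop only for futility does not inflate the error. For example, stopping whenever the interim trend is negative leaves an upper-tail false-positive rate of 0.0247, against the nominal 0.025.

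**4. Thresholds that restore 5% at t = 0.5.**

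- O'Brien-Fleming (critical values c/√t, then c): c = 1.977, so 1.977/√0.5 = 2.797 at the look. That is P<0.0052, then P<0.0480.
- Haybittle-Peto: P<0.001 at the look, then P<0.0498.
- Pocock: P<0.0294 at each look.

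These values hold only at t = 0.5. At t = 0.4 the O'Brien-Fleming form has c = 1.967 and 1.967/√0.4 = 3.110, so P<0.0019 then P<0.0492.

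With a final level of 0.0480, the formula in step 1 becomes (1.977 + 0.842)² × 0.2694 / 0.0256 = 83.6, that is 84 per group instead of 83.

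**5. Who knows what.** Group codes conceal which treatment is which. They do not conceal the size of a difference between the two groups. Coding protects less if the keeper of the random sequence is also the person who acts on the results.

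**The case against.** The strongest reply is that the text does not describe a comparative or unblinded look. It names no interim efficacy endpoint, hypothesis test or early stop, and a review of conduct or safety is not excluded. The article is also condensed, and interim boundaries commonly sit in an analysis plan that is not shown.

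Much of this stands, and it rules out several stronger readings that a reader might infer:

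- **That the investigator certainly sees comparative results.** This is an inference. It is the natural reading, since between-group methods are described just before, but it is not stated.
- **That the look is unblinded.** The Blinding section gives the statisticians group codes only, so on its face any comparison would be coded. The text does not say that the primary researcher who keeps the random sequence is the principal investigator.
- **That the design can be changed without limit.** The ethics committee must accept any protocol change. That limits design changes, but it neither controls the error rate nor stops interim knowledge from spreading.
- **That the error rate is 8.3%.** This holds only if efficacy could be claimed mid-term at P<0.05, and no passage provides for that. No passage excludes it either.
- **That ratings or dosing will be biased.** Those who recruit, dispense and assess are to be blind, and nothing says that the investigator rates patients or passes results on. The route is possible, not shown.

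The appeal to an unseen plan does not dispose of the point. A boundary in an analysis plan could repair the threshold. It would not change the arrangement written in the protocol, in which the trial's own investigator decides on measures in light of interim results.

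**Conclusion.** The concern holds in conditional form. The protocol fixes a mid-term look, a decision maker inside the trial and one flat threshold, and it does not confine the look to data that would be harmless for that person to see.

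If the arms are compared and efficacy can be claimed at P<0.05, the overall two-sided error is about 8.3% at 50% information and about 9.1% at an assumed 25%. These figures assume one between-group test per look and approximately normal test statistics. If the look is pooled, or serves only safety or futility, the error rate is not inflated.

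The risk from interim knowledge does not depend on an efficacy stop. It arises whenever results by group, even coded, reach the investigator while half the participants are still to be recruited and rated. It is greater if the investigator also holds the random sequence, which the documents leave open.

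**What to change.** **Preferred.** State that the mid-term analysis uses pooled, blinded data only (recruitment, dropout, data quality, adverse events), with no between-group efficacy comparison. This costs no alpha; the investigator gives up a comparative look.

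**Otherwise.** State that:

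- an independent statistician runs the comparison;
- one prespecified boundary applies, matched to the actual information fraction, for example O'Brien-Fleming (at 50% information P<0.0052, then P<0.048);
- the investigator is told only whether to continue or that the boundary was crossed;
- the random sequence is held away from the decision maker.

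The cost is a marginally stricter final threshold, about one participant per group by the plan's own formula.

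**If the look has already taken place.** Recruitment ran from January 2018 to a planned end of about June 2020, so with even accrual (an assumption) half was reached around spring 2019, before publication in March 2020. Report what was compared, who saw it and what was decided. If the arms were compared with efficacy stopping possible, test the final analysis at the stricter level: 0.048 at 50% information, recalculated if the fraction differed.

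Each route needs one paragraph in the protocol or analysis plan and, as a protocol change, an application to the ethics committee.
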